## **12.6. SECONDARY ENDPOINTS**

- Renal Replacement Therapy dependency at day 60
- Time-to-Mortality through day 28
- Number of ventilator free days (VFD) at day 28
- Time-to-Mortality through day 60 for the Severe Septic patient(s)

Definitions for secondary endpoints are provided in Appendix D

For renal replacement therapy dependency, treatments will be compared on the number and percentage of patients with the incidence of the event using the Z test for proportions or the continuity-corrected z-test for proportions, depending on event rate. For time-to-mortality through day 28 and for time to mortality through day 60 for the severely septic patient sub-population, treatments will be compared using the log-rank test. For number of VFD at day 28, the sample size, mean, standard deviation, median, quartiles, and minimum and maximum will be presented for each treatment group. Treatment groups will be compared using the two-sample t-test. Health Economic endpoints are still under development will be discussed in a separate plan. These endpoints are not intended to support a PMA application.

In order to control the overall two-sided level of significance at 0.05 across the secondary endpoints, the Benjamini-Hochberg procedure will be used. For time-to-mortality analysis, patients who did not die will be censored at the time of analysis (day 28 or day 60) or at the time of premature withdrawal, whichever is earlier. Otherwise, given the secondary nature of these endpoints, no imputation for missing data will be performed; i.e., patients prematurely withdrawing prior to the time point at which the endpoint is measured will be excluded from the

analysis on that endpoint.

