### **6.2. RANDOMIZATION**

A centralized randomization system has been established with 24-hour availability to provide a mechanism to randomize subjects and enroll them in the study. Once the patient meets all eligibility criteria, **including being on CRRT**

**for a minimum of 4 hours, but no longer than 24**, and has signed informed consent, the site will enter the patient into the randomization system.

Patients will be randomized in a 1:1 allocation utilizing a random permuted block design into either the control or treatment arm, stratified by study center and the presence of severe sepsis or not. (Appendix C). This should occur as close to the start of the Observation period as possible while also allowing time for baseline tests and data to be completed before the patient has been on CRRT for 24 hours. Patients will then be considered enrolled in the study and given a study number. Randomization results will not be revealed to the clinical team and patient until immediately prior to start of first treatment.

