## 12.2. DETERMINATION OF SAMPLE SIZE

The efficacy null and alternative hypotheses to be assessed are as follows:

$$H_0: \lambda_{C+S} = \lambda_C$$

vs.

$$H_1: \lambda_{C+S} \neq \lambda_C$$

where  $\lambda_{C+S}$  and  $\lambda_C$  are the true 60 day mortality hazard rates for the CRRT+SCD and CRRT alone groups, respectively. The null hypothesis will be tested at the overall two-sided 0.05 level of significance at 80% power. Under the assumptions:

1.  $\lambda_C = 0.01155$  when time to mortality is measured in days (leading to a 50.0% mortality rate at 60 days for CRRT alone);  $\lambda_{C+S} = 0.00718$  when time to mortality is measured in days (leading to a 35.0% mortality rate at 60 days for CRRT + SCD);
2. As described in the SCD-003 Protocol, CytoPherx has assumed a mortality rate of 50% for control and 35% for SCD.

For the control mortality estimate, a 2004 publication [20] was used which summarized mortality data for subjects with acute renal failure (ARF) requiring renal replacement therapy (RRT) in the intensive care unit. A table from this publication is reproduced below (Table 9). In this table, the mortality of subjects who received CRRT (“Dialysis”) is compared to those who did not (“% Mortality No Dialysis”). A weighted average was calculated by weighting the observed value for “% Mortality Dialysis” by the number of subjects enrolled. We found that the weighted mortality of subjects who received CRRT was 58.3%, based on this literature analysis of 5,810 subjects.

| Variable          | Ref. | Year | N    | Location                    | % Mortality No Dialysis | % Mortality Dialysis |
|-------------------|------|------|------|-----------------------------|-------------------------|----------------------|
| Brivet et al      | [26] | 1996 | 360  | Multicenter, France         | 43%                     | 64%                  |
| Liano et al       | [5]  | 1998 | 748  | Multicenter, Spain          | 53%                     | 79%                  |
| De Mendonca et al | [27] | 2000 | 1411 | 16 countries, Europe        | NA                      | 44%                  |
| Silvester et al   | [28] | 2001 | 299  | Multicenter, Australia      | NA                      | 47%                  |
| Metniz et al      | [7]  | 2002 | 839  | Multicenter, Austria        | 39%                     | 63%                  |
| Clermont et al    | [29] | 2002 | 254  | Pittsburgh, USA             | 23%                     | 57%                  |

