Then the required evaluable sample size is 166 subjects per group. To account for attrition, which is expected to be minimal, 172 subjects per group will be randomized. The sample size was calculated using the PASS 2008 software, taking into account the fact the study may be stopped for overwhelming efficacy at the interim analysis using the log-rank test at the O'Brien-Fleming significance level of 0.00305.

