#### 12.5. PRIMARY ENDPOINT

The primary endpoint in this trial is time to mortality through 60 days post-randomization. The Kaplan-Meier curve of time (days) to mortality through 60 days post-randomization will be presented, as will the Kaplan-Meier estimate of the 60 day mortality rate. In addition, the raw number and percentage of subjects who died by 60 days will be presented by treatment group. Treatment groups will be compared on time to mortality through 60 days using the log-rank test. The analysis will be carried out for the ITT (primary) and Per-Protocol (secondary) analysis set. It is anticipated there will be few randomized subjects who prematurely withdraw from the trial. Subjects who do not die will be censored at 60 days or at the last known time alive, whichever is earlier.

Due to one formal interim efficacy analysis following which the DSMB may recommend an increase in sample size (based on the observed treatment difference seen at the interim analysis) beyond the initially planned 172 randomized patients (see Section 12.8 for details), the final analysis comparing treatments on the primary endpoint does not use the conventional log-rank test p-value to determine if a statistically significant treatment difference exists. Instead it uses a weighted test statistic,  $T^*$ , proposed by Cui, Hung and Wang [33] in which the independent test statistics of the two stages (interim and final) are combined by pre-specified weights,  $w_1$  and  $w_2 = 1 - w_1$ , where  $w_1$  is the proportion of the total *initially* planned number of patients at which the interim analysis is performed. In the present case the trial is designed for 172 randomized subjects per group with an interim analysis after 50% of the patients achieve 60 day follow-up (or would have achieved 60 day follow-up had they not died or prematurely withdrawn). Thus, the planned information time proportions are  $w_1 = 50\%$  for first stage and  $w_2 = 1 - w_1 = 50\%$  for the second stage.

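### Section 12.6 tests the two mortality secondaries with ordinary log-rank tests although the sample size may be set by the interim mortality difference; the error inflation is small, but the promised overall 0.05 is not guaranteed

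*Protocol*

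**What the plan says.** Protocol section 12.8 plans one interim analysis at 50% of patients. Unless the trial stops, a new sample size is computed as N = (E0/E)² × 172, where E is the observed interim difference in 60-day mortality and E0 the design difference. The planned number is a floor. If the formula asks for more than twice plan, the DSMB may recommend going on to twice plan.

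Section 12.5 draws the consequence for the primary endpoint: "the final analysis comparing treatments on the primary endpoint does not use the conventional log-rank test p-value". It substitutes T*, which combines the two stages with fixed weights of √0.5 each, and it defines T* for the primary outcome only. The remark that simulations confirm type I error control (12.5, 12.8) concerns the same comparison.

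Section 12.6 gives day-28 mortality and the severe-sepsis endpoint the ordinary test: "severely septic patient sub-population, treatments will be compared using the log-rank test". Benjamini-Hochberg is then applied across four secondaries with a stated purpose: "In order to control the overall two-sided level of significance at 0.05 across the secondary endpoints". No weighted statistic, no adjusted level after an early stop and no gatekeeping behind the primary endpoint is stated.

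**The concern.** A death by day 28, or a death in a severely septic patient, is also a death by day 60. The first-stage statistics of these two secondaries are therefore correlated with the interim difference that determines N. The ordinary log-rank test weights patients by the final N, so the weight of the first stage depends on its own result. The protocol accepts this argument for the primary endpoint and then leaves two endpoints built from the same deaths unprotected. A multiplicity procedure cannot repair p-values that are distorted before they enter it.

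At stake is whether a positive secondary mortality result in this pivotal, open-label trial can be presented as controlled at the stated level. Section 12.6 names the test and makes the promise, so this is a stated rule rather than a detail left to an analysis plan.

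**Working it through.** **1. Reproducing the design.** Section 12.2 fixes the level and power ("The null hypothesis will be tested at the overall two-sided 0.05 level of significance at 80% power"). The assumed hazards are 0.01155 ("leading to a 50.0% mortality rate at 60 days for CRRT alone") and 0.00718 ("leading to a 35.0% mortality rate at 60 days for CRRT + SCD"), with 1:1 allocation (6.2). HR = 0.00718/0.01155 = 0.622. Schoenfeld events = 4(1.960 + 0.842)²/(ln 0.622)² = 139, or 140 at level 0.049. Dividing by the mean event probability 0.425 and by 2 gives 164-165 per group, within 3% of the plan ("Then the required evaluable sample size is 166 subjects per group"). Lan-DeMets O'Brien-Fleming spending at information 0.5 gives 0.00305 and 0.0490, as stated. The number 172 is read as per group, following 12.2.

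**2. The enlargement rule on the Z scale.** With 86 per group at the interim and 50% mortality, the standard error of the difference is √(0.5/86) = 0.0762. The 15-point design effect is then Z = 0.15/0.0762 = 1.97. N rises when E is below 15 points and reaches the cap of 344 when E is below 15/√2 = 10.6 points.

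**3. Correlation with the interim difference.**
- Day-28 mortality: the control hazard gives 1 − exp(−0.01155 × 28) = 0.276 by day 28, so the correlation is √(0.276/0.50) = 0.74.
- Severe sepsis: the share is not in the protocol. With 30-80% assumed and equal mortality in and out of the subgroup, the correlation is √0.30 = 0.55 to √0.80 = 0.89.

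**4. Error of one test at nominal two-sided 0.05, no treatment effect, re-estimation only** (normal-scale simulation, 4 million runs per setting).

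| Correlation | Ordinary, planned N kept on adverse trend | Ordinary, formula applied in both directions | Weights √0.5 |
|---|---|---|---|
| 0.55 | 0.051 | 0.053 | 0.050 |
| 0.74 (day 28) | 0.052 | 0.055 | 0.050 |
| 0.90 | 0.054 | 0.058 | 0.050 |
| 1 (the primary itself) | 0.055 | 0.060 | 0.050 |

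A patient-level log-rank check (60,000 trials, standard error 0.0009) gave 0.053-0.054 for day 28 and 0.053-0.055 for severe sepsis at a 50% share.

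**5. Direction of the bias given the interim result.** This is the chance of rejection under no further effect, for a test perfectly correlated with the interim difference.
- E = 5 points, Z = 0.656: N is capped at 344, so the first stage carries fraction 86/344 = 0.25. The ordinary test rejects with probability 0.034, against 0.018 with N fixed at 172: anti-conservative.
- E = 12 points, Z = 1.574: N = (15/12)² × 172 = 268.75, fraction 0.32. The probabilities are 0.098 and 0.116: conservative.
- The two cross near 9.5 points (Z about 1.25).

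**6. The promised family level.** Under the global null, Benjamini-Hochberg over four secondaries gives a family error of 0.046-0.049 with fixed N and 0.048-0.054 with adaptive N. The range reflects assumed correlations with ventilator-free days and RRT dependency and the handling of adverse trends. If three secondaries are truly affected and rejected, the fourth is compared with (4/4) × 0.05 = 0.05, so a null mortality endpoint in that position carries the whole inflation of its single test.

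**7. Early stopping, a separate source.** Take a real primary effect (interim mean Z 1.4, that is 1.4 × 0.0762 = 10.7 points) and a null secondary, with the secondaries tested at 0.05 after any stop. The weighted test still runs at 0.053-0.060 with the efficacy stop alone, and at 0.057-0.069 if adverse trends also stop the trial. When the multiplicity level after an efficacy stop is lowered to 0.00305, a check of 2 million runs per setting (interim mean Z of 0, 1.4 and 2.0) gave a single-test error at or below 0.05 within simulation error.

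**The case against.** A reader might infer that the p-values are too small whenever N has been enlarged. The protocol's rule does not produce that. Step 5 shows the bias reversing above about 9.5 points, and at an interim mean Z of 2.0 with the formula applied in both directions the ordinary test ran at about 0.0485. The inflation holds on average under the null and comes from weak interim trends.

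A reader might also infer that the promised 0.05 is certainly breached. The promise is for the family, not for a single test, and under the global null the family error straddles 0.05. The upper figures need enlargement applied even when the trend is adverse, a case in which 12.8 instead allows a futility stop. They also depend on an assumed sepsis share, and re-estimation has an effect only if the DSMB adopts an increase. Materiality is therefore low: 0.1-0.8 percentage points per test from re-estimation alone.

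All of this stands as to size. It does not remove the inconsistency. Nothing in 12.6 ensures the stated control, and the configuration with three true effects carries the full single-test excess. It is a separate matter that Benjamini-Hochberg targets the false discovery rate rather than the family-wise level.

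**Conclusion.** The point holds as a modest inconsistency. Section 12.5 judges the ordinary log-rank p-value unsuitable after this adaptation, while 12.6 uses it for two endpoints that share the deaths driving the adaptation. Under no effect and from re-estimation alone, the single-test error is about 0.052-0.055 for day-28 mortality and 0.051-0.058 for severe sepsis, against 0.050 with fixed weights. The family error of about 0.048-0.054 means that overall 0.05 is not guaranteed; it does not show that it is always exceeded. Testing at 0.05 after an early stop adds an excess that the weights do not cure. The figures rest on a 30-80% severe-sepsis share, correlations derived from the design hazards, 172 read as per group, and a DSMB that follows the formula when the trend favours SCD.

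**What to change.** In section 12.6, state that each of the two mortality secondaries is tested by combining the statistic from the interim cohort with the statistic from all later patients, using the same prespecified √0.5 weights as T*. Computing the second statistic directly from later patients avoids needing a separate information ratio for the sepsis subgroup. For consistency, treat the other two secondaries in the same way; ventilator-free days also depend on deaths, because Appendix D sets them to zero for patients who die before day 28. Enter these p-values in the multiplicity procedure and report the conventional ones descriptively.

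State separately that, after an early efficacy stop, the multiplicity procedure for the secondaries is run at an overall level of 0.00305 instead of 0.05.

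Both rules should be written before the interim result is known. The cost is a paragraph of text, a few lines of code, and slightly less efficient secondary tests when N is enlarged, because later patients are down-weighted.

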## **4. STUDY DESIGN**

This is a two-arm, randomized, open-label, controlled multi-center Pivotal study.

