### **7.2. TREATMENT DISCONTINUATION CRITERIA**

#### **7.2.1. CLINICAL CRITERIA**

Patients may be withdrawn from therapy (control or treatment) prior to hour 168 for a variety of reasons. When therapy is discontinued prior to hour 168, the follow-up period will immediately begin and data will continue to be collected per protocol.

The Principal Investigator will assign a primary reason for therapy termination utilizing the following categories, and if appropriate, one or more subcategories:

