### 12.3. ANALYSIS POPULATIONS

Intent-to-Treat (ITT) Analysis Set: All randomized subjects. **This is the primary analysis set on which primary and secondary efficacy endpoints will be evaluated.** All subjects will be analyzed according to the treatment to which they were randomized.

Per-Protocol Analysis Set: The subset of subjects from the ITT analysis set in whom randomized treatment was initiated, who received the treatment to which they were randomized, who did not violate the inclusion/exclusion criteria, and who did not prematurely withdraw from the study (except due to death) by 60 days post-randomization.

Safety Analysis Set: The subset of ITT subjects in whom treatment was initiated.

This is the primary analysis set for the safety analysis. Subjects will be analyzed according to treatment received.

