### **NUMBER OF VENTILATOR FREE DAYS (VFD) AT DAY 28**

Ventilator Free Days (VFD) to day 28 is defined as the number of days of unassisted breathing to day 28 after randomization, assuming a patient survives for at least two consecutive calendar days after initiating unassisted breathing and remains free of assisted breathing. If a patient returns to assisted breathing and subsequently achieves unassisted breathing prior to day 28, VFD will be counted from the end of the last period of assisted breathing to day 28 unless a period of assisted breathing was less than 24 hours and the purpose of assisted breathing was a surgical procedure. If the patient is receiving assisted ventilation at day 28 or dies prior to day 28, VFD will be zero (0).

Unassisted breathing is defined as breathing with a face mask or nasal prong oxygen (or room air) following extubation, T-tube breathing, breathing with continuous positive pressure (CPAP  $\leq 5$  cm H2O), or tracheotomy mask breathing.

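### Two of the four secondary endpoints (RRT dependency at day 60 and ventilator-free days at day 28) are observed-case results, although Section 12.3 places secondary endpoints on all randomized subjects

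*Protocol*

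**What the plan says.** Section 12.3 of the protocol defines the ITT set as every randomized subject and says of it: "This is the primary analysis set on which primary and secondary efficacy endpoints will be evaluated". It adds: "All subjects will be analyzed according to the treatment to which they were randomized".

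Section 12.6 lists four secondary endpoints and gives two rules for patients who leave early.

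- **Time to mortality (through day 28, and through day 60 in severe sepsis):** "patients who did not die will be censored at the time of analysis (day 28 or day 60) or at the time of premature withdrawal"; the earlier of these times applies. These patients stay in the analysis.
- **The rest (RRT dependency at day 60, VFD at day 28):** "Otherwise, given the secondary nature of these endpoints, no imputation for missing data will be performed", and "patients prematurely withdrawing prior to the time point at which the endpoint is measured will be excluded from the" analysis of the endpoint concerned.

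The four endpoints are tested with a Benjamini-Hochberg procedure intended to hold a two-sided 0.05 level across them.

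For the primary endpoint, Section 12.5 adds a sensitivity analysis on the ITT set in which missing 60-day mortality status is multiply imputed (10 data sets). No counterpart is stated for the secondary endpoints.

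**The concern.** An analysis that leaves out some randomized patients is not an analysis of all randomized patients. Read together, 12.3 and 12.6 let an observed-case result for RRT dependency or VFD be reported as ITT.

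The label matters because of how patients can be lost. Section 4 states: "This is a two-arm, randomized, open-label, controlled multi-center Pivotal study". Section 6.2 reveals the allocation to the team and patient just before first treatment, when the patient is already randomized. Section 6.1 expects most patients to be unable to consent, so a surrogate often decides, and Section 7.2.2 ends all study activity once consent is withdrawn. Withdrawal can therefore follow knowledge of both the arm and the clinical course. If sicker patients are withdrawn more often in one arm, that arm's mean VFD is too high and its RRT dependency rate is shifted. Both endpoints belong to the formally tested secondary family, and the protocol names no check that would show the problem.

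**Working it through.** **Inputs from the protocol**

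- Section 12.2: 166 evaluable and 172 randomized per group. Allowance: 172 − 166 = 6 per group, and 6/172 = 3.5%.
- Section 12.2: hazards 0.00718 and 0.01155 per day, 60-day mortality 35% and 50%.
- Appendix D: VFD is 0 for a patient who dies before day 28 or is ventilated at day 28.

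**The plan's own figure.** The hazard ratio is 0.00718/0.01155 = 0.622. Schoenfeld's formula at two-sided 0.049 and 80% power gives 140 events. Divided by the mean event rate (0.50 + 0.35)/2 = 0.425, that is 329.4 patients, or 165 per group. A log-rank simulation with 166 per group and the planned interim look gave 79.7% power (8,000 runs). The 166 is reproduced, so 6 per group is a fair reading of the attrition the plan expects.

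**RRT dependency, worst case.** Let the true rates be equal, with k dependent patients among 172 in each group, and let w withdraw from each. In one arm every withdrawn patient would have been dependent; in the other, none.

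- Observed rates: (k − w)/(172 − w) and k/(172 − w).
- False difference: w/(172 − w), whatever k is.

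| w per group | False difference | z, assumed rate 10% (k = 17) | z, assumed rate 20% (k = 34) |
|---|---|---|---|
| 6 (planned) | 6/166 = 3.6 points | 1.18 | 0.84 |
| 9 (about 5%, assumed) | 9/163 = 5.5 points | 1.87 | 1.29 |
| 17 (about 10%, assumed) | 17/155 = 11.0 points | 4.24 | 2.60 |

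The dependency rates are assumptions. The table also takes all 172 patients as having an RRT status, while Appendix D does not say how deaths are classified. If only survivors counted, 50% mortality would leave 86 per group and the bound at w = 6 would be 6/80 = 7.5 points. At the assumed 10% and 20% rates (k = 9 and 17 of 86), z would be 1.80 and 1.25, still below 1.96.

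**VFD, one-arm scenario.** Suppose all 6 withdrawals fall in one arm and each would have scored 0. With an assumed true mean of 10 and SD of 10 (neither is in the protocol):

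- Observed mean in that arm: 10 × 172/166 = 10.36, a rise of 0.36 days. For assumed means of 8 and 12 the rise is 0.29 and 0.43.
- Standard error of the difference: 10 × √(2/172) = 1.08 days. The rise is 0.36/1.08, about one third of it.
- Two-sided type I error: P(|Z + 0.335| > 1.96) = 6.3%.
- With twice the planned attrition (7%, assumed): 10/0.93 − 10 = 0.75 days, and 10.7%.
- With 17 withdrawals and a mean of 8 to 12: 0.9 to 1.3 days.

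This is a scenario, not a bound. The VFD counterpart of the RRT worst case has 6 withdrawn patients who would score 0 in one arm and 6 who would score 28 in the other. That gives 6 × 28/166 = 1.01 days, still under one standard error.

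**When the effect vanishes.** If withdrawal is unrelated to outcome, the expected shift is zero. Equal numbers withdrawn are not enough by themselves: the RRT worst case has equal numbers.

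**The case against.** The strongest reply is that the sections do not conflict. Section 12.3 names a set and requires analysis by randomized arm. Section 12.6 says what happens when a value within that set is missing, confines the exclusion to the endpoint concerned, and gives a reason. That is fair as a reading of intent, and the choice is open rather than hidden. What stands against it is that 12.3 makes all randomized subjects the basis for secondary endpoints with no observed-data qualifier. Section 12.6 also settles the matter by ruling out imputation, so this is not a detail left to a statistical analysis plan.

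The second reply is that few patients are exposed, and this stands.

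- A patient who stops therapy early is not lost: "the follow-up period will immediately begin and data will continue to be collected per protocol" (Section 7.2.1).
- An interruption of more than six hours, or withdrawal from the observation period alone, leaves the patient in follow-up (Sections 7.1 and 7.2.2).
- Section 7.2.1 groups withdrawal of life support with death, and a death before day 28 scores 0 VFD.

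What remains is mainly full withdrawal of consent, which the protocol expects to be rare.

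Third, a patient ventilated at withdrawal has no known day-28 VFD. Only the status at withdrawal is lost, and a score of 0 is an assumption. This also stands.

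A reader might infer that every secondary endpoint drops withdrawn patients. Section 12.6 does not support that for the two mortality endpoints. A reader might also infer that the type I error for VFD is 6.3% or 10.7%. Those figures need all withdrawals in one arm, all scoring 0, and an assumed mean and SD; the second also needs twice the planned attrition.

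**Conclusion.** The point holds in a limited form. RRT dependency at day 60 and VFD at day 28 are observed-case analyses under a fixed rule, and 12.3 should not present them as covering all randomized subjects. Bias arises only if withdrawal depends on outcome in a way that differs between arms. The open-label design and surrogate consent make that possible; nothing in the protocol shows that it is likely.

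At 6 of 172 per group, the worst case is about 3.6 points on RRT dependency, given an RRT status for all 172. That alone would not create significance at assumed rates of 10 to 20%. The one-arm VFD scenario gives about 0.36 days at an assumed mean of 10. At an assumed 10% withdrawal, the RRT worst case reaches 11 points and would. The documents do not support calling the planned analysis invalid, nor do they require imputation as the main analysis, since the primary endpoint itself has it only as a sensitivity analysis. This is a minor improvement: a clearer label and one pre-stated check.

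**What to change.** 1. **Section 12.3:** state that RRT dependency at day 60 and VFD at day 28 are analyzed in ITT subjects with observed data, by randomized arm. Keep this as the main analysis.
2. **Section 12.6:** add a named sensitivity analysis of both endpoints on all randomized patients, extending the multiple imputation of 12.5. Use randomized arm and last known ventilator and RRT status as predictors. Sections 6.4 and 6.5.1 already collect ventilator status daily through the observation and early follow-up periods, and RRT status in early follow-up.
3. **Appendix D, first:** reconcile the definition of RRT dependency before imputing it. It now describes a patient who is not receiving RRT, the reverse of its title, and does not say how deaths are classified.

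The cost is a few sentences, a little programming of a method already planned, and reliance on an imputation model for a few patients per arm.
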